##### Data analysis

Interviews will be analyzed using qualitative content analysis as described by Mayring [60]. The qualitative content analysis consists of nine steps for analyzing texts: (1) determination of the material, (2) analysis of the original situation, (3) formal characteristics of the material, (4) determination of the direction of the analysis, (5) theoretical differentiation of the question, (6) determination of the analysis techniques and definition of the concrete process model, (7) definition of the analysis units, (8) analysis steps using the category system (abstract explication and structuring) and review of the category system of theory and material, and (9) interpretation of the results in the direction of the question and application of content-analytical quality criteria. The Mayring concept is based on reducing the initial material and is, therefore, suitable for large amounts of data and systematic textual processing, as is the case in this work. Although it cannot be used for an explorative-interpretive analysis [61], the concept is well suited to answering the questions posed in this project.

#### Evaluation of interprofessional collaboration

Clinical employees will assess the effects of the approach on interprofessional collaboration and on the understanding of their own role within their team.

##### Sample and sample size

All 120 team members of the medical, nursing, administration, psycho-social and therapeutic professions at the Department of Thoracic Oncology, University Hospital Heidelberg will receive oral and written information on the MCA project with the request to participate. Participants will then receive a written invitation to participate in the study, including the background information, participation details, and informed consent form.

##### Data collection

With the invitation, participants are asked to complete an attached questionnaire prior to the first training within the MCA project (t0), directly after the implementation phase (t1), and 6 (t2) and 12 (t3) months after the implementation phase.

##### Instrument

The German version of the University of the West of England Interprofessional Questionnaire (UWE-IP-D) will be used to assess interprofessional collaboration and attitudes on teamwork of the healthcare professionals [62, 63]. UWE-IP-D is a self-report instrument consisting of 34 items in a set of four scales addressing different themes. It is administered at different stages in training and education. We used three of the four scales: communication and teamwork scale, interprofessional interaction scale, and interprofessional relationships scale. Communication and teamwork items will be measured on a four-point Likert scale (1 strongly agree, 2 agree, 3 disagree, and 4 strongly disagree) leading to sum scores between 9 and 36, with scores 9–20, 21–25, and 26–36, respectively indicating a positive, neutral, or negative self-assessment of communication and teamwork skills. Interprofessional interaction and interprofessional relationship items are assessed on a five-point Likert scale (1 strongly agree, 2 agree, 3 undecided, 4 disagree, and 5 strongly disagree). The interprofessional interaction scale takes sum scores between 9 and 45, with scores 9–22, 23–31, and 32–45, respectively, indicating positive, neutral, and negative perceptions of interprofessional interaction. Sum scores on the interprofessional relationships scale vary between 8 and 40, with scores 8–20, 21–27, and 28–40, respectively, indicating positive, neutral, and negative attitudes towards the respondent’s own interprofessional relationships.

Additionally, healthcare professionals will report gender and profession (nursing, medical, psycho-social, therapeutic, administrative, or other allied healthcare profession).

##### Data analysis

All the characteristics of the healthcare professionals will be analyzed descriptively. Categorical variables are given as absolute and relative frequencies. UWE-IP-D sum scores will be described as means with standard deviation and as median with interquartile range, minimum, and maximum. Differences between assessments will be analyzed using repeated-measures analysis of variance (ANOVA).

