**Methods/design:**

A multiphase mixed-methods design will be used for the study. A total of 100 patients and 120 healthcare professionals in a specialized oncology hospital will be involved. The training outcomes will be documented using a questionnaire. Implementation context and outcomes will be explored through semi-structured interviews and written questionnaires with healthcare professionals and with the training participants and through a content analysis of patient files. Patient outcomes will be assessed in a pragmatic non-blinded randomized controlled trial and in qualitative interviews with patients and caregivers. Trial outcomes are supportive care needs (SCNS-SF34-G), quality of life (SeiQol and Fact-L), depression and anxiety symptoms (PHQ-4), and distress (Distress Thermometer). Qualitative semi-structured interviews on patients’ views will focus on shared decision-making, communication needs, feeling empathy, and further utilization of healthcare services. Interprofessional collaboration will be explored using the UWE-IP-D before the implementation of MCA (t0) and after 3 (t1), 9 (t2), and 12 (t3) months.

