##### Data analysis

All baseline patient characteristics will be analyzed descriptively. Continuous variables will be described as means with standard deviation or as medians with interquartile range, minimum, and maximum. Categorical variables will be described in absolute and relative frequencies.

The sum of the health system and information dimension score of SCNS-SF34-G is defined as the primary outcome of the RCT. The primary outcome at t1 will be analyzed using a linear model in which the outcome value is included as dependent variable and the respective baseline value and the treatment group as independent variables. Missing values in the primary outcome will be replaced by multiple imputation, which consider treatment the group and primary outcomes at t0 as independent variables using the fully conditional specification method [57]. A complete case analysis will be performed as an additional sensitivity analysis. The respective parameter estimates will be reported together with *p* values and 95% confidence intervals. The analysis of the primary outcomes at t2 and t3 will be done analogously to the primary linear model. The analyses of the secondary outcomes will be performed using linear (for continuous outcomes) or generalized linear models (for binary outcomes). The models include the outcome value at follow-up time t1, t2, or t3 as the dependent variable. The respective parameter estimates will be reported alongside descriptive *p* values and 95% confidence intervals. *p* values smaller than 0.05 will be considered statistically significant. Analysis will be done using the statistical software SAS v9.4 (SAS Institute, Cary, NC).

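### The staff survey on collaboration has two schedules that cannot both hold, and its repeated-measures ANOVA, if run in classical form, would use only staff who answer all four waves

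*Protocol article*

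**What the plan says.** Interprofessional collaboration is one of the four study aims, and the UWE-IP-D questionnaire is its only quantitative measure.

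- **Abstract, Methods/design:** the questionnaire is given "before the implementation of MCA (t0) and after 3 (t1), 9 (t2), and 12 (t3) months". The point from which these months are counted is not named.
- **Evaluation of interprofessional collaboration, Data collection:** t0 comes ahead of the initial training session. The later waves come "directly after the implementation phase (t1), and 6 (t2) and 12 (t3) months after the implementation phase". The length of the implementation phase is not given here or elsewhere.
- **Same part, Sample and sample size:** the people asked to take part are "All 120 team members of the medical, nursing, administration, psycho-social and therapeutic professions" at the department.
- **Same part, Data analysis:** "Differences between assessments will be analyzed using repeated-measures analysis of variance (ANOVA"). Nothing is said about staff who miss a wave, and no procedure or software is named for this analysis.
- **Randomized trial, Data analysis:** "Missing values in the primary outcome will be replaced by multiple imputation". This covers the trial's primary outcome and is not extended to the staff survey.

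**The concern.** There are two issues.

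First, the article gives the assessment times twice, and the two versions differ. A reader cannot tell what interval the later collaboration results refer to, and the team running the survey could send a wave at the wrong time. The abstract is not simply repeating the patient schedule, which is 3, 6 and 12 months.

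Second, the named analysis in its textbook form works on complete sets of four scores and assumes equal variances of all pairwise differences between waves (sphericity). Sphericity is harder to defend when waves are unequally spaced. Participation is voluntary, consent can be withdrawn and follow-up runs for a year or more, so some missed waves are likely. A complete-set analysis would then lose precision and describe those who stayed and kept responding.

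**Working it through.** **Timing**

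Inputs: abstract waves at 3, 9 and 12 months; Data collection offsets of 0, 6 and 12 months from the end of implementation. Let D be the unstated length of the implementation phase in months. The Data collection section then implies t1 = D, t2 = D + 6, t3 = D + 12.

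Solving for D at each wave, with the abstract counted from the start of implementation:

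- t1: D = 3 − 0 = 3
- t2: D = 9 − 6 = 3
- t3: D = 12 − 12 = 0

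No single D fits. With D = 3, the Data collection section gives 3, 9 and 15 months against the abstract's 3, 9 and 12. If the abstract is instead counted from the end of implementation, t3 agrees at 12, but t1 (3 against 0) and t2 (9 against 6) do not.

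The gaps between waves do not depend on the time origin:

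| Gap | Abstract | Data collection |
|---|---|---|
| t1 to t2 | 9 − 3 = 6 | 6 − 0 = 6 |
| t2 to t3 | 12 − 9 = 3 | 12 − 6 = 6 |
| t1 to t3 | 12 − 3 = 9 | 12 − 0 = 12 |

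Two of the three gaps differ whatever the anchor, so the contradiction is certain. The 15-month figure is conditional on D = 3.

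**Analysis**

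The plan has no sample size, power or response rate for the staff survey, so there is no stated figure to reproduce. The only input is 120 invited staff. The per-wave response rate r is an assumption. Two patterns bracket the number with all four waves:

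- independent response at each wave: 120 × r⁴
- the same people always respond: 120 × r

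| Assumed r | Independent | Same people always |
|---|---|---|
| 95% | 120 × 0.8145 = 98 | 114 |
| 90% | 120 × 0.6561 = 79 | 108 |
| 80% | 120 × 0.4096 = 49 | 96 |
| 70% | 120 × 0.2401 = 29 | 84 |
| 60% | 120 × 0.1296 = 16 | 72 |

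Under independence, the number with at least one form is 120 × (1 − (1 − r)⁴): about 120, 119 and 117 at 80%, 70% and 60%. That is how many people a mixed model could draw on, although someone with a single form adds little about change within a person. If the same people always respond, a mixed model gains nobody.

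One simulated data set of 120 staff with 80% independent response illustrates the mechanism: 118 people gave at least one form and 44 gave all four. A classical repeated-measures ANOVA routine refused the unbalanced data, while a mixed model used all 363 forms.

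**The case against.** The case against is strongest on the analysis. The plan names repeated-measures ANOVA but never says that staff with a missing wave are discarded. A reader might infer that it does; the text does not support that, because a repeated-measures model fitted by likelihood keeps them. Handling of missed waves, covariance structure and sphericity corrections are details that an article commonly leaves to the full protocol or analysis plan. The survey is observational, has no stated alpha or power, and the article describes its samples as suited to initial exploration. All of this stands, so silence about missed waves is not itself a fault. What remains is that the article does name a method, that its classical form has the limits described, and that a better-suited one is readily available.

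A reader might also infer that the analysis would rest on a minority of staff. That is not established. Even under independence, complete respondents fall below half of the 120 only if r is under 0.5^(1/4), about 84%. People who answer once also tend to answer again, which moves the result towards the higher column.

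On timing, a reader might conclude that the last wave is at month 15. The documents do not say so: the abstract names no anchor and the implementation length is not given. It follows only if implementation lasts 3 months. The mismatch in gaps does not need that assumption.

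**Conclusion.** The schedule contradiction is certain and rests on the text alone: 3 against 6 months between t2 and t3, and 9 against 12 between t1 and t3. Month 15 against month 12 for the last wave is the reading that makes two of the three follow-up waves agree, and it depends on an unstated 3-month implementation phase.

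The analysis point is conditional. If the ANOVA is run in its classical form, it restricts the survey to staff with all four waves and assumes sphericity. The size of the loss cannot be derived from the documents. At assumed per-wave response of 80%, 70% or 60%, between 49 and 96, 29 and 84, or 16 and 72 of 120 would be complete, taking all 120 invited staff as the base.

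Both points touch a stated study aim and are worth correcting. Neither affects the primary analysis or sample size of the randomized trial.

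**What to change.** 1. State one schedule with one named time origin, identically in the abstract and in the Data collection section of the collaboration survey, and give the planned length of the implementation phase. The investigators must say which spacing is intended; the article does not settle it.
2. Replace the repeated-measures ANOVA with a likelihood-based linear mixed model on all available questionnaires, with wave as a categorical factor and an unstructured covariance within person. Report the contrasts of t1, t2 and t3 with t0, each with a 95% confidence interval. This removes the need for complete sets and for sphericity.
3. State that the model is valid under missing-at-random and does not remove bias from non-random non-response. Report the number responding at each wave.

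The cost is a few sentences and a different procedure in standard software; SAS is already used for the trial analysis. No new data are needed.

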### Data integration

A framework analysis will be used to integrate the data from the quantitative and qualitative research collected from different teams of researchers [64]. The following steps are taken: familiarization with the material, identifying a thematic framework, indexing, charting, mapping, and interpretation [64, 65]. Emerging themes will be related to a priori identified domains [32, 64, 65]. Findings from all the phases will be merged using an integrative analysis [35].

### Ethical aspects

Written informed consent will be obtained from each participant. Ethical approval has been given by the Ethics Committee of the University Hospital Heidelberg (S-561/2017). Participants can withdraw their consent at any time. Only investigators will have access to the final trial dataset. There are no contractual agreements that limit such access. Personal information and the confidentiality, coding, security, and storage of the data are in line with German privacy protection law (Bundesdatenschutzgesetz or BDSG) and the privacy policy of University Hospital Heidelberg.

## Discussion

In routine practice, the care of and communication with patients with a limited prognosis is still characterized by discontinuity and lack of coordination. Inadequate communication makes coping with the realities and choices of a complex incurable disease more difficult. A longitudinal communication approach with a focus on the disease trajectory that comprises specific milestones can serve to integrate early palliative care into routine practice and can facilitate care that is individualized to patients’ needs and preferences. While there are international guidelines for advanced cancer care [3, 7], comprehensive implementation strategies are still lacking. As many structural and organizational aspects of national healthcare systems differ substantially, any transfer of guidelines to the German healthcare system should happen according to the specific situation and needs in Germany.

The MCA project includes the conceptualization of a communication strategy that focuses on a process in which patients and their caregivers are equally involved. The improved communication support should foster prognostic awareness and therefore, facilitate advance care planning and end-of-life decision-making.

### Expected impact

The structured integrated tandem approach (physician and nurse) with interprofessional training and coaching is innovative. Consequently, the strengthening of interprofessional collaborations can be expected. The stepwise approach of the MCA project supports the communication skills and strategies of interprofessional healthcare teams involved in the care of patients with a limited prognosis. It will also enhance patients’ quality of life and improve the continuity and coordination of care. The mixed-methods design will provide a detailed insight into this context, including the perspectives of professionals, patients, and their caregivers.

### Limitations and strengths

A strength of this study is that it simultaneously embeds implementation and evaluation, using a strong design (randomized trial) to assess outcomes. The mixed-methods process evaluation will help in gaining a comprehensive understanding of what works and why. The weaknesses of the quantitative methods are balanced by the qualitative methods and vice versa. This exploration of a complex intervention is characterized by multiple methods and multiple stakeholders in two phases. This complexity requires a mix of researchers from different research fields with experience in qualitative and quantitative research. The phases of the MCA project build upon each other. Determining the degree to which MCA is implemented in a real-world setting will give a better understanding of the measured effects. Adaption of the interventions throughout the implementation will ensure the practicability and transferability into everyday practice.

The sample sizes of the different investigations are small but sufficient for an initial exploration of MCA in a real-world setting. However, for a definitive assessment of the effectiveness of MCA, a larger multicenter RCT is necessary. Since the same physicians will be treating patients in the intervention arm as well as the control arm, there is a potential for bias and cross-contamination between the trial arms. However, the nurses participating in the milestone conversations and offering follow-up for patients and caregivers are exclusively in the intervention arm. Our primary end point is a subjective (non-blind) patient-reported outcome, so there is a potential for bias since patients know they are in a trial and they know the purpose of the trial.

Implementing MCA and identifying relevant determinants will be explored using the example of metastatic lung cancer patients. Positive effects will be used to implement an applicable version of the concept to other medical facilities and patients with a limited prognosis.

### Trial status

The beginning of recruitment for phase 2 and phase 3 is planned for May 2018, and will be completed approximately by November 2019.

## Abbreviations

ANOVA: Analysis of variance
BDSG: Bundesdatenschutzgesetz
FACT-G: Functional Assessment of Chronic Illness Therapy: general
FACT-L: Functional Assessment of Chronic Illness Therapy: lung cancer
FCS: Fully Conditional Specification
GAD-2: Generalized Anxiety Disorder: short form (two questions)
MCA: Milestones Communication Approach
MI: Multiple imputation
NCCN: National Comprehensive Cancer Network
NCT: National Center for Tumor Diseases
PDCA: Plan-do-check-act
PHQ-2: Patient Health Questionnaire: short form (depression)
PHQ-4: Patient Health Questionnaire: short form (four questions)
RCT: Randomized controlled trial
SAS: Statistical Analysis Systems
SCNS-P&C-G: Supportive Care Needs Survey for Partners and Caregivers
SCNS-SF34- G: Supportive Care Needs Survey: Short Form for Patients (German version)
SEIQoL-Q: Schedule for the Evaluation of Individual Quality of Life
SPSS: Statistical Package for the Social Sciences
UWE-IP- D: University of the West of England Interprofessional Questionnaire: Interprofessional
